## **7. PARTICIPANT IDENTIFICATION**

### **7.1. Trial Participants**

The Investigator will determine trial participant eligibility based on the criteria given below.

### **7.2. Inclusion Criteria**

The participant may enter the trial if ALL of the following apply:

- Unilateral primary knee replacement, including both total knee replacement (TKR) or unicompartmental knee replacement (UKR), for end stage osteoarthritis
- American Society of Anaesthesiologists (ASA) Grade I to III
- Participant is willing and able consent for themselves
- Male or Female, aged 18 years or above.
- In the Investigator's opinion, is able and willing to comply with all trial requirements

### **7.3. Exclusion Criteria**

The participant may not enter the trial if ANY of the following apply:

- Allergy or intolerance to amide type local anaesthetics
- Objective evidence of nerve damage in the affected lower limb.
- Rheumatoid arthritis
- Any other significant disease, disorder or condition which, in the opinion of the Investigator, may either put the participants at risk because of participation in the trial, or may influence the results of the trial, or the participant's ability to participate in the trial.
- Participants who have participated in another research trial involving an investigational product in the past 6 months.
- Participants who have significant cognitive impairment or language issues
- Contra-lateral knee replacement within the trial or within 12 months prior to randomisation

294 If the patient is receiving staged bilateral knee replacement, they may still participate in the trial but data  
295 will only be included from the first knee.

## 296 **8. TRIAL PROCEDURES**

### 297 **8.1. Patient Identification and Recruitment**

298 All patients listed for knee replacement, i.e. TKR and UKR, for end-stage osteoarthritis will be eligible.  
299 We expect to recruit a maximum of 10% of UKRs as this would reflect current practice in the UK.

300 Patients will be identified via two possible methods:

301 1. Patients will be identified at outpatient clinics by participating surgeons and their clinical care team.  
302 Potential patients will then be seen by the local research nurses/physiotherapist to discuss the study  
303 further and the PI or designee will confirm eligibility.

304 2. Potential patients may also be identified by the clinical team from surgical waiting lists. These patients  
305 will be sent an invitation letter and asked to contact the local team if they are willing to discuss the study  
306 further.

307 Potentially eligible patients will be given an invitation letter and information sheet explaining why they  
308 have been approached. The research team will discuss the study details with the patient. If patients are  
309 willing to proceed into the study, the research nurse or clinician will ask the patient whether they agree  
310 to consent at that time or need up to a week to discuss with family or friends and agree on an  
311 arrangement to confirm their decision.

312 If a further appointment is necessary for the patient to return to give consent and complete the baseline  
313 assessment, all efforts will be made to ensure this appointment is as convenient for the patient as  
314 possible and may coincide with their pre-operative assessment appointment. The pre-operative  
315 assessment appointments are routinely scheduled for a short time before the patient's scheduled  
316 operation date.

317 Data related to the number of potential patients identified and approached will be recorded on  
318 screening logs. The screening log will also depict the number of patients who, once assessed, are  
319 deemed ineligible and also those who decline to participate. Reasons for eligible patients not  
320 participating will be requested, but do not have to be given. Screening logs will not contain patient  
321 identifiable information.

### 322 **8.2. Informed Consent**

323 Informed consent will be taken by a medically-qualified and suitably experienced investigator. All  
324 delegates must be authorised by the Chief/Principal Investigator to obtain consent. The Investigator is  
325 responsible for ensuring that the trial consent procedures comply with current applicable GCP  
326 Regulatory and ethical requirements. The Investigator must be satisfied that the patient has made an  
327 informed decision before taking consent.  
328

The participant must personally sign and date the latest approved version of the Informed Consent Form before any trial specific procedures are performed. Consent will be verbally re-confirmed on the day of surgery.

Written and verbal versions of the Participant Information and Informed Consent will be presented to the participants detailing no less than: the exact nature of the trial; what it will involve for the participant; the implications and constraints of the protocol; the known side effects and any risks involved in taking part. It will be clearly stated that the participant is free to withdraw from the trial at any time for any reason without prejudice to future care, and with no obligation to give the reason for withdrawal.

The participant will be allowed as much time as wished to consider the information, and the opportunity to question the Investigator, their GP or other independent parties to decide whether they will participate in the trial. The patient and the Investigator must personally sign and date the current approved version of the informed consent form in each other's presence. A copy of the signed Informed Consent will be given to the participant. The original signed form will be retained at the trial site.

### **8.3. Randomisation, Blinding and Code-breaking**

Randomisation will be performed locally by the trial site using a secure online internet based system (RRAMP) provided by the Oxford Clinical Trials Research Unit (OCTRU).

Patients will be randomised 1:1 to the two treatment groups using stratified randomisation with variable block sizes, stratified by trial hospital and surgical procedure (TKR or UKR).

Due to local patient pathways, informed consent and baseline assessments may be completed at the same hospital visit however, it may be the case randomisation is not performed on the same day. Where possible, randomisation will occur on the day of surgery either by a member of the clinical research team or a member of the surgical team, where this is not possible randomisation may occur on the days prior to surgery to allow for time to coordinate the drug supplies and inform the operative and anaesthetic team. If consent has occurred more than a day before randomisation, the local research team will verbally check the patient still agrees to participation before proceeding with randomisation.

Only trial team members listed on the delegation log are authorised to perform randomisations.

Patients will be blinded to the treatment allocation. Trial sites should make every effort to ensure that patient blinding is maintained throughout the duration of the trial so that no bias is introduced. The arrangements for maintaining patient blinding for the trial should be considered in detail and those arrangements carefully planned, documented and communicated to ensure accidental unblinding is avoided.

Methods for ensuring patient blinding should be discussed during the Site Initiation Visits, and may include only recording the drug given (active/control) in the surgeon notes as "as per protocol of SPAARK trial" but the actual drug given recorded in the anaesthetic chart. Local practice may vary and the trial sites can discuss with the central study team alternative ways to ensure that patient blinding is maintained.

Unblinding will be performed on an individual basis as clinical need dictates.

#### 8.4. Baseline Assessments

Prior to randomisation the following information will be collected:

- Patient demographics (gender, age at surgery, body mass index)
- Summary medical history
- Summary medication history (current medication and duration of current medication, changes to current medication in the last 6 months, any history of prior opiate use)
- Quality of Recovery 40
- Pain Visual Analogue Scale (0-10) at rest
- Oxford Knee Score
- Clinical Assessment - American Knee Society Score
- Patient expectations of treatment
- Summary healthcare and social services use as well as informal care in the past 6 months due to knee (GP visits, outpatient visits, allied healthcare contacts, hospital admissions, medications, meals on wheels, and unpaid care)
- Summary employment history (in paid employment, not in employment, time away from work or usual activities)
- EuroQol EQ-5D-5L

#### 8.5. Subsequent Assessments & Visits

Following surgery (day 0) and the 3 days following (days 1, 2 and 3) in the evening, the following information will be collected:

- Quality of Recovery 40
- Pain Visual Analogue Scale (0-10) at rest
- Cumulative opiate use (refer to patient medical notes)
- EuroQol EQ-5D-5L

Routine clinical assessments will also occur at the in-patient stage, including assessment of fitness to discharge. This information will be recorded for trial purposes.

Once discharged, patients will be seen again as per local routine clinical care. The Central Study Office will post questionnaires to patients for completion at 6 weeks post-surgery, and at 6 months and 1 year following randomisation. The following information will be collected:

- Summary medication history (since last assessment)
- Quality of Recovery 40
- Pain Visual Analogue Scale (0-10) at rest
- Oxford Knee Score
- Clinical Assessment - American Knee Society Score
- Summary healthcare and social services use as well informal care in past period due to knee (GP visits, outpatient visits, allied healthcare contacts, hospital admissions, medications, meals on wheels, and unpaid care)
- Summary employment history (in paid employment, not in employment, time away from work or usual activities)
- EuroQol EQ-5D-5L

If the patient does not return the postal questionnaire within 7 days, another questionnaire will be posted as a reminder. Following this, if we have not received a completed questionnaire within 14 days, all patient reported data will be recorded over the telephone.

An assessment table is provided in Appendix B.

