## 6.3. Patient Participation

Patients will be involved for a maximum of 12 months post-randomisation. Post operatively, patients will be asked to complete Quality of Recovery-40 assessment daily and a visual analogue scale (VAS) pain score 0-10 on the evening of surgery (day 0) and on days 1, 2 and 3 following surgery. The analgesia requirements of each patient will be recorded. The time of surgery for the patient will be noted. The day of surgery will be called Day 0.

If the patients are discharged home prior to 72 hours postoperatively, then a phone call will be made daily to the patient to collect pain VAS and QoR-40. Pain VAS will be collected by asking the question 'How painful has your operated knee been over the past 24 hours on a scale of 0-10?' The EQ-5D-5L section of the questionnaire will also be completed over the telephone if deemed appropriate. If the patient cannot be contacted between those hours, then an additional call will be made between 2pm and 6pm and this will be noted.

Fitness for discharge will be assessed as per routine clinical care on the evening of surgery (day 0) day 1, 2 and 3 following surgery, until the patient is deemed fit for discharge. This is assessed against the following criteria:

- Ability to mobilize independently
- Pain score less than or equal to 3cm on a 10cm VAS

- Ability to straight leg raise
- Ability to bend knee to 90 degrees

Once discharged, patients will be assessed as per routine clinical care. The Central Study Office will post questionnaires to patients for completion at 6 weeks post-surgery, and at 6 months and 1 year following randomisation. The local hospital research team should encourage timely completion of questionnaires if these time points coincide with the routine follow up appointments. Assessments will include completing the Quality of Recovery 40, Oxford Knee Score, American Knee Society Score and EQ-5D-5L. In addition, an analgesic history will be taken.

A trial flowchart is provided in appendix A.

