### 9.6. Concomitant Medication

The trial and control drug are locally acting and no systemic interactions with other drugs have been reported. Local research teams will record any pain relief medication administered post-operatively. The opportunity to record any variants of the standard medications listed below will also be provided on the CRFs. Sites are not required to record concomitant medication outside of those listed below. Both the trial and control drug will be made up to volume using saline 0.9%. Liposomal bupivacaine must not be diluted with water or other hypotonic agents as it will result in disruption of the liposomal particles.

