#### 9.6.1. Post-Operative Analgesia

Post-operative opioid consumption will be captured on the In-patient CRF. The management of post-operative pain may vary across each participating centre. Local post-operative analgesic regimes must be discussed and approved by the Chief Investigator prior to site activation.

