| Secondary | 
To assess other markers of recovery both in the short term and the long term.
 
To evaluate cost-effectiveness compared with the current standard of care.
 
Safety
                                                                                                     | 
 
• Pain score measured using a 0-10 VAS at baseline and evening of surgery (day 0) and days 1, 2 and 3 following surgery and at 6 weeks, 6 months and 1 year post-randomisation.
 
• QoR 40 Score at baseline and evening of surgery (day 0) and days 1, 2 and 3 following surgery and at 6 weeks, 6 months and 1 year post-randomisation.
 
• Cumulative opioid consumption over 72 hours following surgery.
 
• Fitness for discharge against pre-defined criteria at evening of surgery (day 0) and days 1, 2 and 3 following surgery
 
• Functional outcome using validated, patient-reported (Oxford Knee Score) and qualitative (American Knee Society Score) outcome scores at baseline, 6 weeks, 6 months and 1 year post-randomisation.
 
• Cost-utility analysis using patient-reported quality of life as the main outcome, obtained using the EuroQol EQ-5D-5L at baseline, 72 hours following surgery, 6 weeks, 6 months and 1 year post-randomisation.
 
• Serious adverse events up to 12 months post-randomisation
 
• Related AEs up to 30 days post-surgery
 
• Intraoperative and inpatient complications.
 
 |

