## 6. ANALYSIS

### 6.1 Outcome Definitions

The **co-primary outcome measures** in this trial are the Quality of Recovery 40 score and the cumulative daily pain score both measured at 72 hours post-surgery.

Quality of Recovery (QoR) 40 score – a five dimension validated patient reported peri-operative recovery score that has been widely used across a range of surgeries including knee replacement and assesses overall post-operative recovery [19]. It consists of 40 items each of which is graded on a five-point Likert scale. Total scores are calculated by summing the individual items. QoR-40 scores range from 40 (extremely poor quality of recovery) to 200 (excellent quality of recovery) [18]. The primary time point will be 72 hours post-surgery.

This outcome will also be measured at 6, 24 and 48 hours post-surgery and at 6 weeks, 6 and 12 months post-randomisation.

Cumulative daily pain score – pain at rest will be measured using a visual analogue scale (VAS) ranging from 0 (no pain) to 10 (worst possible pain). Measurements taken as close as possible to 6, 24, 48, and 72 hours post-surgery will be included in the primary outcome assessment. This outcome will also be measured at 6 weeks, 6 and 12 months post-randomisation.

The **secondary outcome measures** in this trial are cumulative opiate use, the Oxford Knee Score, the American Knee Society Score, fitness for discharge, and the co-primary outcome measures at additional time points. The health economics outcomes in this trial include summary medication history, EQ-5D-5L, summary healthcare and social services use, and summary employment history.

Cumulative opiate use – all opioids used on evening of surgery (day 0) and days 1, 2, and 3 will be recorded and a running total of cumulative opioid use calculated. A list of acceptable opioids is provided in the trial protocol.

Fitness for discharge – this will be assessed against pre-defined criteria on evening of surgery (day 0) and days 1, 2, and 3 following surgery as per routine clinical care. Patients will be considered fit for discharge when they meet four criteria: (i) ability to mobilise independently; (ii) pain score less than or equal to 3 on a 10 score VAS scale; (iii) ability to straight leg raise; and (iv) ability to bend knee to 90 degrees. It will also be recorded whether patients were discharged, and if they were not discharged when fit for discharge the reasons for this will be collected.

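### The 72-hour opioid total has no named data source and no specific missing-data rule once a patient goes home before 72 hours

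*Combined protocol and SAP*

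**What the plan says.** SAP 2.2 (Table 1) defines the endpoint over a fixed window: "Cumulative opioid consumption over 72 hours following surgery". The assessment table in Protocol Appendix B schedules it on each of post-operative days 0, 1, 2 and 3.

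The protocol names two places where the data come from. The day 0 to 3 list in Protocol 8.5 has "Cumulative opiate use (refer to patient medical notes", and Protocol 9.6.1 says "Post-operative opioid consumption will be captured on the In-patient CRF".

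Protocol 6.3 foresees discharge before 72 hours and provides for it: "a phone call will be made daily to the patient to collect pain VAS and QoR-40". EQ-5D-5L may be added to that call. Opioid use is not on its list. The next medication history is the 6-week questionnaire, a summary that nothing links to the 72-hour total.

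SAP 6.1 says that all opioids used on days 0 to 3 will be recorded and "a running total of cumulative opioid use calculated". SAP 6.2 analyses the result as one value per patient, by linear regression (after transformation if needed) or, failing normality, by an unadjusted non-parametric method. SAP 6.3 has specific imputation or sensitivity rules for QoR-40, pain, OKS and AKSS, including one for missing pain scores in patients already discharged. It has no specific rule for opioids.

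**The concern.** A total over a fixed 72 hours needs data for all 72 hours from every patient. Medical notes and an inpatient form cannot be relied on to hold tablets that a patient takes at home. Of the four items that Protocol 8.5 lists for days 0 to 3, opioid use is the only one tied to the chart and the only one that the post-discharge call does not cover.

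The gap opens at discharge, and discharge is something the treatment may change: Protocol section 4 suggests that liposomal bupivacaine may let patients go home earlier. If the intervention arm did leave sooner and home doses went unrecorded, the error would favour the hypothesis and would not be random noise. What is at stake is the reading of one secondary outcome, although reducing opioid use is a recurring theme of the protocol's rationale.

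**Working it through.** **Figures in the plan.** The documents give no opioid total, opioid SD or discharge rate, so there is no stated opioid figure to reproduce. The one planned number used below is 250 per arm (Protocol 11.2, SAP 3.3), which agrees with its own inputs: 240 / 0.96 = 250 and 225 / 0.90 = 250.

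**Assumptions, none of them from the documents.** True 72-hour use is equal in the two arms. Home doses are omitted. Nobody is home in the first 24 hours. The proportions home during 24–48 h and 48–72 h are h2 and h3. The shares of total use falling in those periods are w2 and w3. Use is either even (w2 = w3 = 1/3) or front-loaded (50/30/20%, so w2 = 0.30 and w3 = 0.20).

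**Formula.** Recorded fraction of the true total: r = 1 − w2·h2 − w3·h3. Spurious relative reduction = 1 − r(intervention) / r(control).

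| Scenario | Control h2 / h3 | Intervention h2 / h3 | Even use: r control, r intervention | Reduction | Front-loaded: r control, r intervention | Reduction |
|---|---|---|---|---|---|---|
| A | 0% / 10% | 0% / 20% | 0.967, 0.933 | 3.4% | 0.980, 0.960 | 2.0% |
| B | 5% / 25% | 10% / 35% | 0.900, 0.850 | 5.6% | 0.935, 0.900 | 3.7% |
| C | 10% / 40% | 20% / 60% | 0.833, 0.733 | 12.0% | 0.890, 0.820 | 7.9% |

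Worked example, B with front-loaded use: control 1 − 0.30×0.05 − 0.20×0.25 = 0.935; intervention 1 − 0.30×0.10 − 0.20×0.35 = 0.900; 1 − 0.900/0.935 = 3.7%.

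**Equal discharge timing.** With 10% / 40% home in both arms and even use, r = 0.833 in each. Both totals are about 17% too low, and the bias between arms is nil.

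**Effect on the test.** A simulation used 250 per arm, log-normal use with an assumed coefficient of variation of 0.8, an unadjusted t-test on the log scale at 5%, and 4,000 runs. With home doses omitted, the false-positive rate in A, B and C was about 10%, 19% and 56% with even use, and 6%, 11% and 27% with front-loaded use. It was about 5% when discharge timing was equal or home doses were captured.

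**If discharged patients are set to missing.** Complete totals would remain for 250×0.90 = 225 against 250×0.80 = 200 patients in A, and for 250×0.60 = 150 against 250×0.40 = 100 in C. Fitness for discharge requires a pain score of 3 or less (Protocol 6.3, SAP 6.1), so those who remain are selected on a post-randomisation state related to opioid need. Any resulting bias has a different mechanism and could run in the other direction.

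**The case against.** The documents state a wider intent than the two inpatient sources suggest. Protocol 6.3 says "The analgesia requirements of each patient will be recorded", Protocol 9.6 has local teams "record any pain relief medication administered post-operatively", and SAP 6.1 does not limit recording to the ward. The CRFs and call scripts are not part of the documents, so sites may ask about home use. This stands as evidence of intent, but none of these statements gives a source or method for the period after discharge.

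Missing data are not ignored. Protocol 11.4 allows multiple imputation as appropriate with sensitivity analyses, and SAP 6.3 promises missingness by arm, with reasons, for every secondary outcome. That also stands. But a total that stops at discharge will not show up as missing unless a rule says that it should.

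The size is uncertain. Protocol section 4 gives an average stay of 3 to 6 days, so scenario C, with about half the patients home before 72 hours, may be too extreme. The illustration gives leavers the same use as those who stay. Given the pain criterion for discharge, leavers may use less, which would shrink the loss. The simulation is also simpler than the planned analysis. Finally, the outcome is secondary, and Table 14 of the SAP will show discharge status by arm and day, so a difference in truncation would be visible.

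A reader might infer that home doses will be counted as zero and that the intervention will therefore look opioid-sparing. The documents do not support that. No section says zero; the handling is undefined. A spurious benefit needs home doses to be omitted, one arm to leave earlier, and material opioid use at home. None of the three is established, and the protocol says only that earlier discharge is possible.

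**Conclusion.** The point holds as a gap in data capture and in the analysis rule. Followed as written, the named sources cannot deliver a 72-hour total for patients who go home early, and the SAP does not say what value those patients receive. Omitting home doses under-counts the total, more so in any arm discharged earlier; treating the patients as missing loses them selectively.

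The between-arm error is about 2% to 12% over the scenarios shown. That range rests wholly on assumed discharge rates and an assumed spread of use, with equal true use and home doses omitted. It illustrates the mechanism and does not predict this trial's bias. The co-primary outcomes, and conclusions drawn from them, are unaffected. The change is worth making because the remedy is cheap and the outcome could otherwise be misread.

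**What to change.** - **Collection.** On the existing daily call, up to 72 hours, ask which opioids were taken since the last assessment and how many. Add a matching CRF field.
- **Derivation.** Compute the 72-hour total from ward plus home use in a common opioid-equivalent unit. SAP 6.1 names no unit for adding different opioids, and it refers to a list of acceptable opioids in the protocol that does not appear in Protocol 9.6 or 9.6.1.
- **Missing data.** State in the SAP that post-discharge periods without data are missing, not zero, and are imputed, with a sensitivity analysis.
- **Reporting.** Show inpatient-only use descriptively, labelled as such.

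The cost is one question on a call already made, one form field and a short SAP paragraph. Sample size does not change. The downside is that home doses are self-reported, so ward and home data will differ in quality.

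Timing matters. The planned trial period ends on 14 August 2021 with 12 months of follow-up, so on that timetable the last randomisation falls no later than mid-August 2020, before SAP V2.0 of 17 December 2020. If the calls are already complete, the SAP rule and the labelling can still be put in place, and any claim about opioid use should be limited to what was captured.
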